## 207 **5.Exclusion and Inclusion criteria**

### 208 **5.1 Inclusion criteria**

209 The inclusion criteria were as follows:

210 (a) untreated adolescent males and females with AIS;

- 211 (b) AIS patients with a primary curve Cobb angle  $>10^{\circ}$  ;
- 212 (c) all subjects aged 9 to 17 years;
- 213 (d) AIS patients with a Risser grade ranging from 0 to 4, with female adolescents
- 214 being within one year post-menarche;
- 215 (e) participants capable of understanding and completing complex motor tasks;
- 216 (f) patients or their parents proficient in using a smartphone.

## 217 **5.2 Exclusion criteria :**

218 The exclusion criteria included:

- 219 (a) a non-idiopathic etiology of scoliosis determined by clinical information, physical
- 220 examination, or medical imaging;
- 221 (b) AIS patients with other spinal disorders (e.g., tumors);
- 222 (c) patients with limb length discrepancy.

## 223 **6.Research process**

### 224 **6.1 The patients' baseline assessment**

- 225 (1) Complete basic information such as height, weight, age, and the Risser grade;
- 226 (2) Whether the individuals have disc herniation, nerve compression symptoms,
- 227 spinal fracture, etc., are determined by X-ray and physical examination;
- 228 (3) Baseline Cobb Angle, ATR, and the gait analysis will be assessed.

### 229 **6.2 Allocation**

230 The patients with AIS will be randomly divided into two groups. The Digital Care  
231 group (n=64) underwent PSSE with the help of a telerehabilitation system. The  
232 Conventional Intervention group (n=64) will experience PSSE three sessions in the  
233 outpatient department of a hospital and complete the home-based PSSE training.

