## 1. Background

Adolescent idiopathic scoliosis (AIS) is a complex three-dimensional spinal deformity of unknown etiology, defined as a spinal curvature of  $\geq 10^{\circ 1, 2}$ . According to scoliosis screening studies conducted between 1985 and 2011, the prevalence of AIS is estimated to be between 0.5% and 5.2%. It is generally accepted that the incidence of AIS among individuals under the age of 16 is approximately 2% to 3%. Among adolescents with a Cobb angle greater than  $20^{\circ}$ , the likelihood of disease progression is 70% or more. According to the recommendations of the International Society on Scoliosis Orthopaedic and Rehabilitation Treatment (SOSORT), conservative treatment should be provided to adolescents with AIS to prevent the progression of scoliosis before skeletal maturity is reached.

Physiotherapy Scoliosis-Specific Exercises (PSSE) are among the most crucial conservative treatments for patients with AIS. Moderate-certainty evidence from multiple randomized controlled trials (RCTs) supports the effectiveness of PSSE in slowing the progression of scoliosis in AIS patients and even reducing the degree of curvature. However, compared to conventional exercises such as resistance training, PSSE requires a deeper understanding by patients of the specific exercises tailored to their type of scoliosis, making mastery more complex and challenging for AIS patients. Additionally, patients with AIS must adhere consistently to a standardized PSSE regimen over the long term and develop habits of daily self-management to ensure the efficacy of PSSE. In previous high-intensity evidence-based trials, the traditional PSSE model involved an initial assessment and 1 to 3 treatment sessions conducted by qualified physiotherapists at outpatient clinics or specialized orthopedic institutions, after which patients completed the PSSE regimen at home without supervision.

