## **2.Research Objective**

The Healbone Intelligent Rehabilitation System (HIRS) is a user-centered smartphone application that integrates remote supervision and guidance of PSSE training with scoliosis-related educational videos and articles. In our previous work, we demonstrated the efficacy of the HIRS system in patients with nonspecific low back pain. The purpose of this RCT is to compare the treatment outcomes of a Digital Care Group (DCG) receiving PSSE supervision and guidance through the HIRS system (Beijing, CN) and educational videos with those of a Conventional Intervention Group (CIG) following the traditional PSSE model.

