## 183 **4.4 The calculation of sample size**

184 The sample size estimation for this study is based on the Cobb angle, which serves  
185 as the primary outcome measure. The sample size was calculated using PASS  
186 11.0 In accordance with the principles of clinical superiority trials and preliminary  
187 trial results, the clinically meaningful difference in the improvement of the Cobb  
188 angle between the DCG and CIG groups is 4, with a standard deviation of 6 for both  
189 groups, and a superiority margin of 4 for the Cobb angle. Assuming a power of 80%  
190 and a two-sided significance level of 0.05, the estimated sample size is 102  
191 participants (51 per group). Accounting for a 20% dropout rate, a total of 128  
192 participants (64 per group) will need to be enrolled.

193

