In this trial, individuals in the DCG group receive a single in-person PSSE training session under the guidance of physical therapists (PTs) in an outpatient setting. During this session, PTs will assist patients or their guardians in installing the HIRS system on their smartphones and provide instructions on how to utilize the system. Simultaneously, individuals with AIS will be required to promptly study educational videos and articles related to scoliosis to enhance their understanding of the conditionError! Reference source not found.. Following this session, individuals in the DCG group will complet home-based PSSE training through the HIRS system. The HIRS system automatically records individual PSSE training performance and engagement data, including the number of sessions and duration of training.

In the Conventional Intervention Group (CIG), individuals will receive three 90-minute in-person training sessions per month, under the guidance of PTs, during the first three months, with additional guidance sessions provided as needed. During these sessions, patients or their guardians are required to record the entire PSSE instructional process on video and received printed PSSE exercise materials. Subsequently, patients with scoliosis will complete the six-month PSSE training regimen at home using these videos and materials.

Figure 2. Example of the HIRS system.

[figure not shown]

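### Sections 6.2 and 6.3 of the protocol give the control group different in-person PSSE contact: three sessions in one, nine plus further sessions as needed in the other

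*Protocol*

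**What the plan says.** Four places in the protocol bear on the control arm, the Conventional Intervention Group (CIG).

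- Section 6.2 (Allocation): "Conventional Intervention group (n=64) will experience PSSE three sessions in the" outpatient department, followed by home training. No monthly rate, session length or period is given.
- Section 6.3 (Intervention): "individuals will receive three 90-minute in-person training sessions per month, under the guidance of PTs, during the first three months". The same sentence then allows for contact beyond this schedule: "with additional guidance sessions provided as needed". No criterion for the additional sessions is stated, and no maximum.
- Section 1 (Background), on earlier trials: "the traditional PSSE model involved an initial assessment and 1 to 3 treatment sessions conducted by qualified physiotherapists at outpatient clinics" or specialised institutions, after which patients exercised at home without supervision.
- Section 2 (Objective): the digital group's outcomes are to be compared "with those of a Conventional Intervention Group (CIG) following the traditional PSSE model". The end of the Background says the same.

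For the Digital Care Group (DCG), Section 6.3 states that "individuals in the DCG group receive a single in-person PSSE training session under the guidance of physical therapists (PTs").

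The sample size in Section 4.4 assumes that the clinically meaningful difference in improvement of the Cobb "angle between the DCG and CIG groups is 4, with a standard deviation of 6 for both" groups. It attributes its assumptions in part to preliminary trial results and does not describe the control schedule behind them.

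**The concern.** In-person contact with a therapist is one of the main things that separates the two arms, since Section 6.3 prescribes the same home exercise regimen for all patients. If the CIG receives three sessions, the trial asks whether app-supported exercise after one session does better than the brief outpatient instruction that the Background calls traditional. If the CIG receives nine or more sessions, it asks whether the app does better than repeated supervised training over three months. A positive or a null result would mean different things in these two trials. The Background motivates the study by scarce therapists and poor access to guidance, and a control arm with nine or more supervised sessions represents that setting less well.

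There are practical consequences too. Two schedules in one protocol could lead to inconsistent delivery. They could also lead to inconsistent classification in the per-protocol analysis named in Section 4.3, if clinic attendance enters its definition. And a reader of Section 4.4 cannot tell which comparator the assumed difference was meant for.

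**Working it through.** **Inputs.** CIG sessions in Section 6.2: 3. CIG rate in Section 6.3: 3 per month for 3 months, 90 minutes (1.5 h) each. DCG in-person sessions in Section 6.3: 1. Background range for the traditional model: 1 to 3.

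**Session count.** Sessions = rate x months. Section 6.3 gives 3 x 3 = 9, before any additional sessions, so 9 is a minimum. Section 6.2 gives 3. The ratio is 9 / 3 = 3.

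**Contact time.** Section 6.3 gives 9 x 1.5 h = 13.5 h. Section 6.2 gives no session length. If 90 minutes is assumed there as well, it gives 3 x 1.5 h = 4.5 h, and the ratio is again 3. The conclusion does not rest on this assumption: for three sessions to supply 13.5 h, each would have to last 13.5 / 3 = 4.5 h.

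**Contrast between arms.** In-person sessions, DCG versus CIG, are 1 versus 3 under Section 6.2 and 1 versus at least 9 under Section 6.3.

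**Can the passages be read together?** There are two ways to read Section 6.2.

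| Reading of Section 6.2 | Against Section 6.3 (at least 9) | Against the traditional model (1 to 3) |
|---|---|---|
| Three sessions in total | conflicts | fits |
| Shorthand for three per month | agrees | hard to square: 9 is three times the upper end |

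Either reading leaves a conflict somewhere. Nothing else in the protocol settles it: Section 7 covers only the follow-up visit, and Section 4.4 names no schedule.

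**Illustration for the per-protocol set.** A CIG patient who attends three sessions has 3 / 3 of the scheduled contact under Section 6.2 and 3 / 9, or one third, under Section 6.3. This matters only if attendance is part of the per-protocol definition, which the protocol does not give.

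**The case against.** The best defence is that Section 6.2 is a two-sentence summary about allocation. It also leaves out the DCG's single session, and Section 6.3 is where number, length, rate and period are set out. On that view, three sessions is loose shorthand for three a month and Section 6.3 governs. The shorthand is possible, but Section 6.2 does not say so, and three in total is what fits the Background. Treating Section 6.3 as governing would still leave the Objective's label in tension with the schedule. The defence softens the conflict between 6.2 and 6.3 and does not remove it.

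It can also be said that the Background reports what earlier trials did and gives no period for its one to three sessions, so it is not a binding definition. That stands. It is why nine or more is called hard to square with the traditional model here, and not flatly incompatible with it.

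Several stronger readings are tempting and should not be drawn:

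- A reader might infer that the 4-degree difference is valid for only one of the two schedules. Section 4.4 ties it to neither. The supportable point is that the basis is not stated.
- A reader might infer that extra control sessions are unlimited. The text says as needed; it is silent on criterion and cap.
- A reader might infer that a mixed comparator will be delivered. This is a single-centre trial with two senior therapists, so inconsistent delivery is only a possibility.
- A reader might infer that the per-protocol analysis is compromised. Its definition may sit in a statistical analysis plan that is not shown, and the adherence measures in the protocol concern home exercise.

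**Conclusion.** Wrong as written: an internal inconsistency in the definition of the control intervention. Scheduled in-person contact is 3 sessions in one section and at least 9 in another, a factor of three or more, with no text that reconciles them. The size in sessions follows directly from the protocol. The size in hours (4.5 versus at least 13.5) also needs the assumption of 90-minute sessions under Section 6.2.

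It would go too far to say that the trial's question as a whole is open. The arms, hypotheses, primary outcome, six-month time point and common home regimen are fixed. What is not fixed is how much supervised contact the control arm receives, and that is enough to change the interpretation of superiority over it. An analysis plan cannot repair this, because the control intervention is for the protocol to define.

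**What to change.** Reconcile the Background, the Objective, Section 6.2 and Section 6.3 so that a single CIG schedule, with session count, length and period, appears throughout. Which schedule that should be is for the sponsor and investigators. Make the comparator's label in the Objective and in the trial's conclusions match the reconciled schedule. In Section 4.4, state which comparator the 4-degree assumption refers to.

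The cost is protocol wording only. Recording each patient's in-person sessions, including the additional ones, and reporting them by arm would be a useful addition for about one case-report field, but it is not the core of this point. If recruitment has already begun, the sponsor can still state which schedule has been delivered.

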### 234 **6.3 Intervention**

235 In this trial, HIRS system will be provided free of charge to AIS patients in the DCG  
236 group, and physical therapists will encourage timely usage of the HIRS system via

smartphone during the six-month study period. HIRS is a smartphone application available for iOS, Android, and local web solutions. For participants without internet access, hotpots will be provided. The HIRS system consists of three distinct components: the physician's interface, the user's interface, and the data storage module, as depicted in Figure 2. A secure and seamless bidirectional connection is established between the physician's interface and the user's interface, supported by technical experts and IT professionals. The study involves two senior rehabilitation therapists, each with over five years of experience in the diagnosis and conservative management of scoliosis. One of the therapists is a member of SOSORT.

Prior to the commencement of the trial, professional healthcare personnel creates specific PSSE training videos, which, along with detailed instructions, were uploaded to the HIRS system. At the start of the trial, the HIRS system was installed on the smartphones of patients in the DCG group, and personal accounts will be registered via the application. During the initial treatment phase, therapists will transmit digital PSSE training protocols to the patients' personal accounts and provide education on the correct usage of the application. Patients are required to access the application via their personal accounts each time they engaged in PSSE training. Upon initiation of the exercises, patients will follow the instructions provided in the video to complete each movement in the training protocol. If a patient failed to engage in the exercises, the system automatically sends a reminder and notifies the PTs, who then contact the patient to determine the cause of non-compliance.

The PSSE training consisted of daily self-correction exercises and over-correction exercises. The daily self-correction exercises were based on the SEAS methodError! Reference source not found., where therapists instructed AIS patients in specific three-dimensional corrective postures in the sagittal, coronal, and transverse planes, aiming to realign the spine to a neutral position. To enhance patient self-management of posture, PTs will require AIS patients to maintain the self-corrective posture during routine activities such as sitting, standing, and walking whenever possible. If patients are unable to actively control their posture continuously, they will be encouraged to utilize aids, such as insoles or cushions, to achieve passive correction. Given that the trial participants are students who spend

the majority of their day in a seated position, seated self-correction exercises formed a significant component of the daily training regimen. All AIS patients perform a minimum of 30 minutes of seated self-correction exercises daily for a duration of six months. The over-correction exercises were derived from the Schroth method. The over-corrective exercise protocols varies according to the PUMCH-SSE classification. During the over-correction training, patients' spines are compelled to maintain a neutral or even over-corrected position. All AIS patients engage in over-correction exercises for 30 minutes per day, at least five days a week, for a duration of six months. The PSSE training regimen, established based on the PUMCH-SSE classification, has been demonstrated to be effective for AIS patients.

In this trial, individuals in the DCG group receive a single in-person PSSE training session under the guidance of physical therapists (PTs) in an outpatient setting. During this session, PTs will assist patients or their guardians in installing the HIRS system on their smartphones and provide instructions on how to utilize the system. Simultaneously, individuals with AIS will be required to promptly study educational videos and articles related to scoliosis to enhance their understanding of the conditionError! Reference source not found.. Following this session, individuals in the DCG group will complet home-based PSSE training through the HIRS system. The HIRS system automatically records individual PSSE training performance and engagement data, including the number of sessions and duration of training.

In the Conventional Intervention Group (CIG), individuals will receive three 90-minute in-person training sessions per month, under the guidance of PTs, during the first three months, with additional guidance sessions provided as needed. During these sessions, patients or their guardians are required to record the entire PSSE instructional process on video and received printed PSSE exercise materials. Subsequently, patients with scoliosis will complete the six-month PSSE training regimen at home using these videos and materials.

Figure 2. Example of the HIRS system.

[figure not shown]

## 7. The follow-up

All participants will come back to Peking Union Medical College Hospital to complete the follow-up (including measuring the Cobb angle and the ATR, completing the gait analysis and so on) after the 6-month intervention.

## 8. The Figure of research proccess

[figure not shown]

311

